## Data Handling and Record Keeping

Data from the questionnaires will be entered electronically and transferred to the Newcastle University Server.

## Access to Data

Direct access may be granted to representatives of the Sponsor, Host Institution or REC for monitoring or auditing purposes.

## Archiving

The Trial Master File (with identifiable data) will be archived by the CI in the University of Newcastle IHS for 10 years. Anonymised individual patient data is made available for sharing at the end of the study. Archiving will be authorised by the Sponsor following submission of the end of study report. The CI will request authorisation from the Sponsor to destroy the documentation at the end of the archiving period.

# MONITORING, AUDIT & INSPECTION

The Trial coordinator completing the monitoring will be independent of the Sponsor and the study team. All monitoring findings will be reported and followed up with the appropriate persons in a timely manner.

The trial may be subject to audit by representatives of the Sponsor. Data from each local authority site will be stored in the central research centre in Newcastle, who will permit trial-related audits, including access to all essential and source data relating to the trial.

A Trial Management Group will be established comprising the Chief Investigator, Senior Co-applicants, Study Statistician, Health Economist, Senior Trial Manager and Research Associates.

A Trial Oversight Committee (TOC) will be established to provide overall supervision of the trial, this group will be approved by the NIHR.

Observers from the NIHR PHR programme and from Sponsor will be invited to all TOC meetings. The committee will meet on three occasions – at the beginning of the study, and at the end of Phases 1 and 2.

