**TRIAL SUMMARY**

| **Trial Title** | **SOLID (Supporting Looked After Children and Care Leavers In Decreasing Drugs, and alcohol):** a pilot feasibility study of interventions to decrease risky substance use (drugs and alcohol) and improve mental health of Looked After Children and Care Leavers aged 12 -20 years |
| --- | --- |
| **Acronym** | SOLID |
| **Summary of Trial Design** | Pilot feasibility randomised controlled trial |
| **Summary of Participant Population** | Looked After Children and Care Leavers (LAC) aged 12-20 years who screen positive for being at risk of early drug and alcohol use (≥ 2 in the CRAFFT). |
| **Planned Sample Size** | Phase 1 Formative Research  20 1:1 interviews with LAC  20 1:1 interviews with Carers  1 focus group with professionals  1 focus group with Drug and alcohol workers  Pre pilot trials  5 1:1 interviews with LAC trialing the interventions  5 1:1 interviews with Drug and Alcohol workers trialing the interventions  LAC leads survey:  Surveys with all named LAC Community Pediatric leads in each local authority in England (n=152).  Intervention finalization workshop  1 focus group with Professionals  1 focus group with LAC and Carers  Phase 2 Pilot RCT  Sample size required - minimum of 35 LAC per arm at follow-up (3 arm trial). Aim to recruit 150 LAC in total to allow for 30% loss to follow-up.  Process Evaluation  20 1:1 interviews with LAC  20 1:1 interviews with Carers  15 1:1 interviews with Drug and alcohol workers  1 focus group with Social Workers  1 focus group with Drug and alcohol workers |
| **Planned Number of Sites** | 5 (Newcastle, Durham and Teesside (Middleborough, Stockton and Redcar) |
| **Intervention Duration** | 6 sessions over a maximum of 12 weeks |
| **Follow Up Duration** | 12 months (+8 week window) |
| **Planned Study Period** | 24 months |

| **Intervention arms** | 2 active intervention arms:   - 6 sessions of Motivational Enhancement Therapy (MET) or - 6 sessions of Social Behavioural Network Therapy (SBNT)   Interventions will take place over a maximum of a 12 week period. |
| --- | --- |
| **Control arm** | Usual social worker delivered care with additional signposting to local drug and alcohol third sector services. |
| **Inclusion criteria** | - LAC aged 12-20 years - Screen positive for at risk of substance misuse i.e. scoring ≥ 2 on the CRAFFT screening questionnaire - Consents to take part in the study |

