# STUDY DESIGN & STUDY SETTING

The proposed research has two linked phases: 1. Formative phase consisting of adaptation and manualisation of the interventions, and a national survey of LAC Clinical Service Leads to help characterise usual care across England and identify potential collaborative centres for a definitive trial. This will be followed by a second phase consisting of a pilot feasibility randomised controlled trial (RCT). This second phase of the project will also have a detailed economic component outlined in section 11.

The two phases are detailed in Sections 5 and 6 respectively and are illustrated in Figures 1 and 2 on pages 26 and 31 respectively

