## Unblinding

The trial statistician and health economist will only be unblinded after the final analysis or if requested to do so due to safety concerns expressed by the Trial Oversight Committee.

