## End of Trial

The end of the trial will be considered as the last participant’s follow-up visit at 12 months.

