## Recording and Reporting AEs and SAEs

All AEs and SAEs occurring from the time of randomisation in the Pilot RCT until follow up is completed (12 months post enrolment) must be reported. Depending on the nature of the event, the reporting procedures below should be followed. Any questions concerning adverse event reporting should be directed to the Chief Investigator or the Study Coordinator (Research Associate) in the first instance.

**Adverse Event (AEs):** All non-serious adverse events (as defined in section 9.1 above and including non-serious adverse reactions) during study participation must be recorded on an adverse event/harms case report form and sent to the Study Coordinator within 2 weeks of the event. Severity of AEs will be graded on a three-point scale (mild, moderate or severe). The Study Coordinator will enter the data onto the study database. In addition, the Study Coordinator will contact the LAC team manager monthly to ensure no adverse events are missed.

Expected AEs include the following:

- Severe drug and alcohol use
- Mental health difficulties
- Self-harm and suicidal ideation

**Serious Adverse Event (SAEs):** All SAEs (as defined in section 9.1 above and including serious adverse reactions) during study participation must be reported to the Chief Investigator within 24 hours of the site becoming aware of the event. The initial report should ideally be made by completing the study SAE form and sending via the fax number listed on page 64 of the protocol. Alternatively, if this is not possible, the initial report may be made by telephone to the number listed on page 64 of the protocol. In the case of incomplete information at the time of initial reporting, all appropriate information should be provided as follow-up as soon as this becomes available. Relationship of the SAE to study procedures will be assessed by the Chief Investigator, as will the expected or unexpected nature of the SAE.

As the study deals with a vulnerable population, expected SAEs include those related to the following which result in hospitalisation:

- Severe drug and alcohol use
- Mental health difficulties
- Self-harm and suicidal ideation

SAEs exclude:

- any pre-planned hospitalisations (e.g. elective surgery) not associated with clinical deterioration
- routine treatment or monitoring of the studied indication, not associated with any deterioration in condition

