***TOC***

- *Review of safety data collected to date to identify any trends*

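### No oversight committee meeting is scheduled between first randomisation and the last 12-month visit, although the committee is assigned the safety trend review

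*Protocol*

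**What the plan says.** Section 13 of the Protocol sets up the committee and its calendar: "A Trial Oversight Committee (TOC) will be established to provide overall supervision of the trial", and "The committee will meet on three occasions – at the beginning of the study, and at the end of Phases 1 and 2".

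Section 9.4 gives the TOC one safety task: "Review of safety data collected to date to identify any trends". Under Section 5.7 the statistician and health economist stay blinded until after the final analysis, with one exception: they may be unblinded "if requested to do so due to safety concerns expressed by the Trial Oversight Committee".

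Section 4 makes the phases sequential, with the formative work first and the pilot randomised trial second. The sentence in Section 9.2 that begins "All AEs and SAEs occurring from the time of randomisation in the Pilot RCT until follow up is completed (12 months post enrolment) must be" makes reporting compulsory over that window. Section 5.10 ends the trial at the last participant's "follow-up visit at 12 months".

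No separate data monitoring committee is described. Figure 5 in Section 8 has a row for meetings of a study steering committee, but that body is not defined elsewhere or linked to the TOC. The row's cells cannot be read in the text available.

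**The concern.** The Protocol assigns a review of accumulating safety data and then schedules the reviewing body only before such data exist and after they are complete. The task in Section 9.4 and the exception in Section 5.7 are both useful mainly while participants are being recruited, treated or followed, and no meeting is set for that time.

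This matters because of how serious events are routed. Section 9.2 lists in advance, as expected, hospitalisations related to severe drug and alcohol use, mental health difficulties, or self-harm and suicidal ideation. It says expectedness is to be judged by that list alone. Such an event would not be classed as an unexpected serious adverse reaction, so it would not go to the ethics committee by the expedited route in Section 9.3. An imbalance between arms in these events would show only in an aggregate table, and the TOC is the only body given the job of looking for trends.

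The calendar also affects conduct. Recruitment and retention are primary outcomes of the pilot (Section 3.3), and the committee charged with overall supervision has no scheduled meeting at which either could still be corrected.

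**Working it through.** **Meetings set against the safety window**

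| TOC meeting (Section 13) | Position relative to the trial | Randomised safety data available | Participants still to be followed |
|---|---|---|---|
| Start of study | Before Phase 1 work | None | None yet randomised |
| End of Phase 1 | Before Phase 2, so before randomisation | None | None yet randomised |
| End of Phase 2 | At or after the last 12-month visit | Complete or nearly so | None, or almost none |

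Scheduled meetings between first randomisation and last 12-month visit: 0. Figure 5 lists analysis and writing-up under Phase 2, so the third meeting may fall later still.

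**Length of the gap**

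Inputs: 24-month study and 12-month follow-up with an 8-week window (Trial Summary); adverse event reporting to 12 months post enrolment (Section 9.2). The length of recruitment, R months, cannot be read from Figure 5.

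- First randomisation to the last participant's 12-month point = R + 12 months, so at least 12.
- Share of the study: 12 / 24 = 50% at the least.
- Upper limit: 24 − 12 = 12 months remain for Phase 1, recruitment and reporting together, so R is below 12 and the gap is below 24 months.
- The 8-week window is 8 × 7 / 30.44 = 1.8 months. It can delay the last visit to R + 13.8 months, but it lies outside the adverse event reporting period, so it is not counted as unreviewed safety time.

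**Numbers involved**

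Section 10.3 reproduces: 35 / (1 − 0.30) = 50 per arm and 3 × 50 = 150 in total, of whom 2 × 50 = 100 are allocated to one of the two therapies.

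**When a review could still affect trial therapy**

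The service contacts a participant within 6 weeks (Section 5.4), and sessions run over at most 12 weeks (Section 6.2). If sessions start at contact, therapy ends about 6 + 12 = 18 weeks after randomisation. Even for the last person recruited, the third meeting then comes about 52 − 18 = 34 weeks or more after therapy has ended.

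**The case against.** The best defence is that safety oversight during the trial does exist. The Chief Investigator reviews risk and benefit continuously, and serious events must reach the Sponsor within 24 hours (Section 9.4). The coordinator contacts the care team manager monthly so that events are not missed (Section 9.2). Unexpected serious reactions go to the ethics committee within 15 days (Section 9.3). Urgent safety measures, including a halt, need no TOC meeting (Section 9.6), and an annual report goes to the ethics committee (Section 14.1). The trial is classed as comparable in risk to standard care (Section 2.1), and Section 9.4 sets no frequency for the trend review.

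All of this stands, and it rules out some tempting readings. A reader might infer that participants are unmonitored for the whole trial; the individual-event routes show otherwise. A reader might infer that the TOC can never meet, or that the exception in Section 5.7 can never be used. The text forbids neither ad hoc meetings nor correspondence, and Section 14.9 requires TOC agreement before study procedures change, which implies contact between meetings. Nor does the list of expected serious events suggest that the therapies cause them: Section 9.2 explains the list by the vulnerability of the population.

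What the defence does not supply is a scheduled aggregate review. The routes listed deal with single events, rest with the trial's own lead, or, like the annual report, are not described as a comparison by arm. The statistician, who sits on the Trial Management Group, is blinded. Low risk justifies light oversight, but not a trend review timed for when it can no longer protect anyone.

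Figure 5 remains open. If its steering committee is the TOC and the row shows Phase 2 meetings, the practical gap narrows, but the figure then contradicts the three occasions in Section 13.

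**Conclusion.** The point holds as one of scheduling. Sections 5.7 and 9.4 give the TOC functions that Section 13 provides no meeting to perform during the randomised trial. The gap is at least 12 months plus recruitment, at least half of the planned study, and covers up to 150 participants. It concerns committee review of aggregate data, not the handling of individual events.

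The conclusion assumes that the phases run in sequence as Section 4 states, that Phase 2 ends no earlier than the trial itself, and that the expected-event list in Section 9.2 governs classification. Section 9.3 words the expectedness test more loosely, as an assessment against known information. The list also covers only events leading to hospitalisation, so a death would not be treated as expected by it. No error rate, power or effect estimate is affected.

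**What to change.** - Amend Section 13 to add at least one TOC meeting or teleconference during Phase 2, timed while participants are still being recruited or treated.
- State that it receives adverse and serious adverse events, recruitment and retention, tabulated by coded arm so that the statistician's blinding is kept.
- Name that meeting in Section 9.4 as a point at which trends are reviewed, and in Section 5.7 as one at which safety concerns can be raised. State also that the TOC may be convened between scheduled meetings.
- Reconcile the steering committee row in Figure 5 with the TOC and with the number of meetings in Section 13, using one name throughout.

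The cost is a small amount of committee time and one short report from data already being collected. No eligibility, treatment or outcome rule changes.

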# ETHICAL AND REGULATORY CONSIDERATIONS

## Research Ethics Committee Review and Reports

The CI will obtain a favourable ethical opinion from an NHS Research Ethics Committee (REC) prior to the start of the trial. Though the study does not recruit from NHS centres, due to the vulnerability of this population and the nature of the difficulties experienced i.e. drug and alcohol difficulties, NHS ethical review will be sought. All parties will conduct the trial in accordance with this ethical opinion.

The CI will notify the REC of all required substantial amendments to the trial and those non-substantial amendments that result in a change to trial documentation (e.g. protocol or patient information sheet). Substantial amendments that require a REC favourable opinion will not be implemented until this REC favourable opinion is obtained. The Sponsor will notify the REC of any serious breaches of GCP or the protocol, urgent safety measures or USARs that occur during the trial.

An annual progress report will be submitted each year to the REC by the CI until the end of the trial. This report will be submitted within 30 days of the anniversary date on which the original favourable ethical opinion was granted.

The CI will notify the REC of the early termination or end of trial in accordance with the required timelines.

## Peer Review

The study has been peer reviewed as part of the NIHR review and funding system.

## Public and Patient Involvement

Three groups of LAC (n=11 aged 12-20 years) have been consulted to develop this proposal and members are interested in developing an ongoing study PPI group. As a result of our PPI, we have changed the target age range of the study from 13-17 to 12-20 years so we do not exclude early substance users or LAC as they transition to adult services. The LAC felt it essential to involve young people in the development of the interventions and felt this research was important, especially with the rise of 'legal highs'. We also consulted widely with services including drug and alcohol workers, social workers and managers. In response to this work, we have amended our strategy for recruiting LAC into the study. LAC and professionals felt that social workers rather than LAC nurses were best placed to screen for substance use.

All our consent and information forms have been shared with young people (LAC and the Young people's advisory group (YPAG) (n=29 aged 12-18). The PPI group will meet regularly during the study and feed into the oversight group.

## Regulatory Compliance

The trial will be conducted in accordance with the Research Governance Framework. Before any site can enrol patients into the trial, that site must have received permission from the site management organisation, in this case the local authority.

## Protocol Compliance

Prospective, planned deviations or waivers must not be used without prior authorisation by the Sponsor. Any protocol deviations identified during the course of the study will be reported as per the NCTU Standard Operating Procedure. Frequently occurring deviations could be considered a serious breach.

## Notification of Serious Breaches to GCP and/or the Protocol

A serious breach is a breach which is likely to effect to a significant degree –

1. the safety or physical or mental integrity of the subjects of the trial; or
2. the scientific value of the trial

The Sponsor must be notified immediately of any incident that may be classified as a serious breach. The [Sponsor/CI] will notify the NHS REC within the required timelines in accordance with the NCTU SOP.

## Data Protection and Patient Confidentiality

All investigators must comply with the requirements of the Data Protection Act 1998 with regards to the collection, storage, processing and disclosure of personal information and will uphold the Act’s core principles.

Researcher administered questionnaires completed by participants online will be identified by the unique study identification code and initials. Only members of the research team will be able to link the unique study identification code to patient identifiable data needed for record linkage and participant contact.

All study records and Investigator Site Files will be kept at site in a locked filing cabinet with restricted access. The Trial Master file will be stored in the Institute of Health and Society, Newcastle University in a locked filing cabinet.

## Indemnity

The Sponsor (Newcastle University) will provide indemnity in the event that trial participants suffer negligent harm due to the management of trial.

The substantial employers of the protocol authors (Newcastle University) will provide indemnity in the event that trial participants suffer negligent harm due to the design of the trial.

The study sites (drug and alcohol service providers) will provide indemnity, as part of their service delivery, in the event that trial participants suffer negligent harm due to the provision of interventions as part of clinical care at their site. Service providers will meet their own service requirements for safety and clinical care.

## Amendments

It is the responsibility of the Research Sponsor to determine if an amendment is substantial or not and study procedures must not be changed without the mutual agreement of the CI, Sponsor and the Trial Oversight Committee.

Substantial amendments will be submitted to the REC and will not be implemented until this approval is in place. It is the responsibility of the CI to submit substantial amendments.

Non-substantial amendments may be made at any time with a record of the amendment held in the Trial Master File. Any non-substantial amendment that requires an update to the trial documentation will be submitted to the NHS REC for acknowledgement of the revised version of the document.

Substantial amendments and those minor amendments which may impact sites will be discussed with the LAC Lead in each local authority. Amendment documentation will be provided to sites by the CI.

## Post-Trial Care

Following the end of the study all LAC will return to usual care.

## Access to the Final Trial Dataset

The TOC will have access to the final full trial dataset if requested. Other researchers that wish to access the data will need permission from the CI, TOC and NIHR.

# DISSEMINATION POLICY

Data arising from the study will be the property of the Chief Investigator and Co-Investigators. Publication will be the responsibility of the Chief Investigator and published under the authorship agreed with the Co-Investigators.

On completion of the study, data will be analysed and tabulated and a final study report prepared. This will be available from the NIHR PHR and FUSE websites.

In addition to the NIHR monograph, it is planned to publish this study in peer review articles and to present data at national and international meetings. Results of the study will also be reported to the Sponsor and Funder, and will be available on their web site. Publications will be shared with the TOC and funders. Individuals will not be identified from any study report. Individuals will not be identified from any study report.

Participants will be informed about their treatment and their contribution to the study at the end of the study, including a lay summary of the results. This will be developed by the study PPI group.

Publication of the results of the study will follow NIHR guidance on communicating research outcomes. NIHR will also receive full citations of research outputs when these become available.

All research reports issued by individual researchers and/or research teams will:

● Credit the NIHR as a funding organisation

● Carry the NIHR disclaimer

Only anonymised data will be used when publishing results; no personal identifiers will be used

